# Medial open transversus abdominis plane (MOTAP) catheters for analgesia following open liver resection: study protocol for a randomized controlled trial

**DOI:** 10.1186/1745-6215-15-241

**Published:** 2014-06-21

**Keywords:** Liver surgery, Analgesia, Transversus abdominis plane, Randomized controlled trial

## Abstract

**Background:**

The current standard for pain control following liver surgery is intravenous, patient-controlled analgesia (IV PCA) or epidural analgesia. We have developed a modification of a regional technique called medial open transversus abdominis plane (MOTAP) catheter analgesia. The MOTAP technique involves surgically placed catheters through the open surgical site into a plane between the internal oblique muscle and the transverse abdominis muscle superiorly. The objective of this trial is to assess the efficacy of this technique.

**Methods/design:**

This protocol describes a multicentre, prospective, blinded, randomized controlled trial. One hundred and twenty patients scheduled for open liver resection through a subcostal incision will be enrolled. All patients will have two MOTAP catheters placed at the conclusion of surgery. Patients will be randomized to one of two parallel groups: experimental (local anaesthetic through MOTAP catheters) or placebo (normal saline through MOTAP catheters). Both groups will also receive IV PCA. The primary endpoint is mean cumulative postoperative opioid consumption over the first 2 postoperative days (48 hours). Secondary outcomes include pain intensity, patient functional outcomes, and the incidence of complications.

**Discussion:**

This trial has been approved by the ethics boards at participating centres and is currently enrolling patients. Data collection will be completed by the end of 2014 with analysis mid-2015 and publication by the end of 2015.

**Trial registration:**

The study is registered with
http://clinicaltrials.gov (
NCT01960049; 23 September 2013)

## Background

### Background and rationale

Liver resection is the optimal treatment for patients with primary or metastatic liver malignancies, benign liver tumours, and some biliary diseases
[1-5]. In Canada, over 2,000 patients annually undergo liver resection, predominantly for cancer
[6]. Over the past few decades, improvements in surgical technique, better haemostatic control, and wider indications for liver resection, especially for those with metastatic disease, has resulted in a significant increase in the prevalence of liver resection surgery. There has been an increase of approximately 12% in the number of liver resections performed each year with a cumulative increase over 5 years of more than 60%
[7].

Due to the location of the liver and the propensity for bleeding during resection, surgery is typically performed through a large right subcostal incision. The subcostal incision, however, is associated with significant postoperative pain and distress which may result in respiratory complications, delayed mobilization and physiotherapy, and prolonged hospital stay
[8]. Inadequate postoperative pain management is associated with the development of chronic postsurgical pain which is costly to both the patient and society
[9-12]. Intense postoperative pain is a risk factor for the development of chronic postsurgical pain (CPSP)
[9-12]. Prolonged pain after surgery is the result of changes in the peripheral and central nervous system causing amplification, increased sensitivity, and prolongation of pain
[13]. It is estimated that as many as 30% of Canadians who undergo an operation will develop CPSP and the severity of acute postoperative pain is a predictor of its development
[14]. Chronic pain is costly to the patient and society in terms of direct health care expenditures, and indirect costs associated with lost productivity, as well as suffering and disability
[12]. Aggressive and effective early postoperative pain relief may prevent the development of chronic pain
[11].

Conventional techniques of postoperative analgesia include epidural catheters, intravenous opioid patient-controlled analgesia, and peripheral nerve blocks
[15-17]. Peripheral nerve blocks - specifically transversus abdominis plane (TAP) blocks - have been described
[18-20]. A modification of the TAP technique which involves surgeon placement of the TAP catheters directly into the open surgical wound (medial open transversus abdominis plane; MOTAP) has been investigated both at Sunnybrook Health Sciences Centre and at the University Health Network – Toronto General Division
[21].

### Epidural analgesia

Epidural analgesia remains the gold standard for pain control following an abdominal surgical procedure
[22]. However, complications from epidural analgesia include hypotension, bradycardia dural puncture, spinal infection, and rarely, but devastatingly, neurological damage
[23-26]. Furthermore, removal of epidural catheters may provide logistic challenges if patients develop coagulopathy on the basis of liver dysfunction
[27-30]. Given the above risks, many institutions do not routinely insert epidurals for patients undergoing major liver resection.

### Intravenous opioid patient-controlled analgesia

Despite the variety of pain-relieving modalities available, postoperative pain following liver surgery is significant and remains a challenge to manage. Opioid analgesia, while effective at rest, fails to provide adequate pain relief associated with movement such as breathing, coughing, ambulation, and gastrointestinal motility
[11,31]. Moreover, opioids are associated with adverse effects such as nausea, vomiting, constipation, sedation, and respiratory depression
[20].

### Transversus abdominis plane

Movement-evoked incisional pain accounts for the majority of pain experienced, and the nerves responsible arise from thoracic levels T6 to T10
[32]. These nerves lie in a plane between the internal oblique and transversus abdominis muscles, known as the TAP
[18,33,34]. The TAP block involves injecting local anaesthetics into this fascial plane, thereby blocking transmission of the sensory neurons responsible for abdominal surgical pain. Afferent sensory information from these nerves can be blocked by infiltrating local anaesthetic via a surgically placed catheter that runs in the lateral TAP (blocking T8 to T10) and extends into a second adjacent anatomical compartment, the posterior aspect of the rectus sheath (blocking T6 to T8). A variation of the TAP block, the oblique subcostal block, provides sensory blockade for surgical incisions between T6 and T10 dermatomes, including the subcostal or chevron incision used in liver surgery
[18]. A retrospective study of 36 patients demonstrated that ultrasound-guided TAP blocks significantly decreased 24-hour cumulative morphine consumption
[19]. A recent randomized controlled trial demonstrated that TAP blocks and epidural analgesia are equally efficacious in controlling postoperative pain
[20]. However, due to the close proximity to the peritoneum and the highly vascularized liver, single-shot subcostal TAP blocks are quite challenging to perform, even under ultrasound guidance, as evidenced by two cases of liver puncture in a sample of 36 patients
[19]. In small studies, TAP blocks decreased postoperative opioid consumption, nausea, and vomiting, while providing pain control similar to epidural analgesia
[35]. TAP blocks are typically infiltrated using ultrasound guidance at the conclusion of the operation. Preliminary uncontrolled studies and case reports have demonstrated the potential efficacy, safety, and patient satisfaction of TAP catheters
[20,36].

### MOTAP technique – modification of the transversus abdominis plane technique

We have recently developed a modification of the TAP technique for regional analgesia following subcostal incisions termed MOTAP catheter placement. This technique involves surgical placement of the catheter under direct vision. During subcostal incision these muscular planes are clearly visible, allowing more confident insertion of a catheter directly into the correct plane
[37]. In a pilot study, 22 fit adults undergoing donor hepatectomies received TAP catheters at the end of surgery. The patients received the first dose of bupivacaine (0.2 cm^3^/kg 0.125%) at the end of surgery and this regimen was repeated every 12 hours until postoperative day 3. We compared postoperative pain scores and opioid use to historical controls and found a significant (*P* < 0.05) difference in cumulative postoperative opioid (hydromorphone) consumption at 48 hours (mean ± SD: 20.8 ± 15.8 mg for MOTAP catheters vs 39.1 ± 25.1 mg for patient-controlled analgesia (PCA)).

### Primary objective

To assess the impact of MOTAP catheters plus intravenous, patient-controlled analgesia (IV PCA) compared to the standard of care (that is, IV PCA alone) on opioid consumption in patients undergoing hepatic resection requiring a subcostal incision.

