### Secondary objectives

To assess the effect of MOTAP catheters on:

1. Postoperative pain intensity.

2. Opioid-related adverse effects, including nausea, vomiting, pruritus, sedation, and postoperative ileus.

3. Time to ambulation, duration of hospital stay and reduced postoperative pain disability.

4. Post-surgical complications (for example, pneumonia).

5. Incidence and intensity of chronic postsurgical pain.

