## Methods/design

### Study design

This is a multicentre, prospective, blinded, randomized controlled trial comparing MOTAP catheters plus IV PCA to standard care (IV PCA alone) in patients undergoing subcostal incision for liver resection. Full inclusion and exclusion criteria for the trial are summarized in Table 
1. The trial has been approved by the Toronto Academic Health Sciences Network Research Ethics Boards from Sunnybrook Health Sciences Centre (178–2013) and from the University Health Network (12-0493-A).

**Table 1 T1:** MOTAP study inclusion and exclusion criteria

**Inclusion criteria**	**Exclusion criteria**
• >18 years of age	• Patients unable to comprehend instructions, consent, or co-operate with pain assessment
• Undergoing liver resection using a subcostal incision (upper midline extension is allowed)	
• Incision extends to allow visualization of internal oblique and transversus abdominis muscles	• Allergy to any study medications
	• Patient not able to be extubated postoperatively for any clinical reason
	• Laparoscopic surgery
	• Co-existing epidural or intrathecal analgesia
	• Chronic pain disorders or on long-term opioids (greater than 1 month prior to operation)
	• History of substance or alcohol abuse
	• Transplant donor liver resections
	Prior right subcostal incision

MOTAP, medial open transversus abdominis plane.

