### Randomization

Patients will be randomized to one of two parallel groups: experimental (local anaesthetic through MOTAP catheter) or placebo (normal saline through MOTAP catheter). Each research pharmacy will have a concealed randomization list and the appropriate syringes will be dispensed by the pharmacy. The code will be retained centrally and only revealed to the investigators once recruitment and data collection is completed. Randomization will be stratified by centre. A brief schema and study outline of this trial is summarized in Figure 
1.

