#### Insertion of MOTAP catheters (both groups)

Following liver resection, the operating surgeon will insert two catheters. The following muscles will be identified: rectus abdominis, transversus abdominis, internal oblique, and external oblique. The surgeon will dissect between the internal oblique and transversus abdominis fascia superiorly to open the TAP. A plane will also be developed between the rectus muscle and the posterior sheath. The first catheter will be placed subcostally in the anterior axillary line, between the transversus and internal abdominal muscles. The second catheter will be sited at the lateral border of the right rectus abdominis muscle, between the posterior rectus sheath and the rectus abdominis muscle. Approximately 10 cm of catheter will be left in each plane, and tunnelled to skin sites distal to insertion. The catheters will be secured under occlusive sterile dressing, and covered with tape. The skin will be closed using either staples or suture at the surgeon’s discretion. The catheter will be fastened to the skin using steri-strips and an occlusive sterile dressing. For the TAP catheter we will use the 001159-20D InfiltraLong 600 T (manufacturer Pajunk, Germany) and we will use a standard three-orifice catheter for the rectus space.

The study lead at each site will be responsible for ensuring that all participating surgeons adhere to this technique of MOTAP insertion. Prior to enrolling a patient, each participating surgeon must perform at least one MOTAP insertion with the site’s lead present to become credentialed in the technique. We will audit the insertion technique of each surgeon at least every five cases to ensure consistency.

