#### Control group – normal saline infusion through MOTAP

At the conclusion of surgery, patients in the control group will have 0.9% normal saline 20 ml bolused then a 5 ml/hour infusion into each catheter.

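### The objective and design name IV PCA alone as the comparator, but every patient receives catheters and the randomised contrast is ropivacaine versus saline

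*Protocol article*

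**What the plan says.** Three statements of purpose treat the catheters as the thing under test:

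- Primary objective: MOTAP catheters plus IV PCA "compared to the standard of care (that is, IV PCA alone) on opioid consumption".
- Study design: "comparing MOTAP catheters plus IV PCA to standard care (IV PCA alone".
- Secondary objectives: "To assess the effect of MOTAP catheters on" pain, opioid adverse effects, ambulation, hospital stay, complications and chronic pain.

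The sections that define the arms describe something else:

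- Abstract, Methods/design: "All patients will have two MOTAP catheters placed at the conclusion of surgery", and "Both groups will also receive IV PCA".
- Randomization: "experimental (local anaesthetic through MOTAP catheter) or placebo (normal saline through MOTAP catheter".
- The insertion section is headed "Insertion of MOTAP catheters (both groups" and describes opening two tissue planes and tunnelling a catheter from each to the skin.
- Control group: "patients in the control group will have 0.9% normal saline 20 ml bolused then a 5 ml/hour infusion into each catheter".
- Postoperative care: both groups are prescribed celecoxib under the same creatinine rule, and all catheters stay in until the morning of postoperative day 3.

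**The concern.** The objective governs the conclusion. As written, a positive trial would be reported as showing that MOTAP plus PCA beats PCA alone, a comparison that no randomised patient informs. The Abstract gives the aim as assessing the efficacy of the technique, and the Discussion looks ahead to a standardised pain protocol and to use in other operations. That decision is whether to place the catheters at all, whereas the trial randomises what goes through them.

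The secondary objectives carry the same problem. If complications, ambulation or stay do not differ between arms, a reader who takes the objective at its word could conclude that the catheters add no harm relative to standard care. The comparison cannot support that, because both arms have them.

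**Working it through.** **1. Components by arm**

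| Component | Objective's comparator (IV PCA alone) | Actual control | Experimental |
|---|---|---|---|
| IV PCA hydromorphone | yes | yes | yes |
| Celecoxib where eligible | not mentioned | yes | yes |
| Dissection and two catheters | no | yes | yes |
| Bolus and infusion volume | none | yes (saline) | yes (ropivacaine) |
| Local anaesthetic | no | no | yes |

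The first column has no randomised patients. The second and third differ in the last row only.

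**2. What each contrast estimates**

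Let R be the mean outcome with ropivacaine through catheters, S with saline through catheters, and P with PCA and no catheters. Then

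R − P = (R − S) + (S − P).

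The objective as worded asks for R − P. The trial estimates R − S. The two agree only if S − P = 0, that is, if dissection, catheters and saline infusion have no net effect on the outcome. The article neither states nor justifies this, and the trial has no data on P.

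**3. The plan's own sample size**

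Inputs (Sample size calculation): mean 39.09 mg, SD 25.07, 40% reduction, two-sided alpha 0.05, power 90%.

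- Difference: 0.40 × 39.09 = 15.636 mg.
- Normal approximation: n = 2 × (1.960 + 1.282)² × 25.07² / 15.636² ≈ 54.0, taken as 55 per group.
- With the noncentral t distribution: 56 per group.
- Power by t-test: 0.915 at 58 per group and 0.923 at 60.

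The stated 58 is within two patients of the recomputed figure, so the arithmetic stands.

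The 39.09 mg does come from 111 patients treated before the catheters were introduced, so it is an estimate of P, used where S is needed. To show what this could mean, hold the experimental mean at 0.60 × 39.09 = 23.45 mg, the SD at 25.07 and n at 60 per group. Then vary S over an **assumed** range that is not in the documents:

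| S relative to 39.09 mg | S − R (mg) | Power |
|---|---|---|
| 20% lower | 7.82 | 0.40 |
| 10% lower | 11.73 | 0.72 |
| equal | 15.64 | 0.92 |
| 10% higher | 19.55 | 0.99 |

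This is illustration only. The documents give no evidence on the size or direction of any such shift.

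**4. What can still be said about the catheters**

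In-hospital complications are recorded in all patients and graded by the Clavien classification (Secondary outcomes), so catheter events can be described over both arms. For example, 0 events in 120 would give an exact two-sided 95% upper limit of 1 − 0.025^(1/120) = 3.0%.

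**The case against.** The real contrast is not hidden. The Abstract, Randomization, the two arm descriptions and Blinding all make clear that this is a placebo-controlled trial with saline through the same catheters. Writing active plus background versus background alone is common shorthand for an add-on trial. MOTAP is also used partly as the name of an analgesic technique that works through local anaesthetic, and a saline control isolates that mechanism and permits blinding. All of this stands, and it is why the design is not at issue. It does not remove the mismatch: the two places that state the comparison both name a comparator that does not exist, and elsewhere MOTAP plainly means the catheter, through which saline is also given.

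A reader might infer more than the documents support:

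- *The trial cannot show catheter-related harm at all.* This goes too far. Catheter events can be described, and harms of the local anaesthetic can be compared between arms. The complications objective gives pneumonia as its example, and the Background links pain to respiratory complications and delayed mobilisation. Ropivacaine versus saline can test effects that act through pain relief.
- *The between-arm difference in catheter-caused complications is zero by design.* That holds only if catheter risk does not depend on what is infused, which the documents do not establish. Only effects common to both arms are invisible.
- *The protocol claims that the catheters are safe.* It does not, and the Discussion makes no such claim. The risk lies in how a null result could be read.

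**Conclusion.** The point holds as a mismatch between the stated comparison and the randomised one. The trial validly estimates the effect of ropivacaine against saline given through MOTAP catheters, on a background of IV PCA and celecoxib where eligible. It does not estimate the effect of adding catheters to PCA unless dissection, catheters and saline are assumed inert.

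The size lies in the scope of the conclusion: the stated objective is one that no arm can answer. The blinded saline control, the *t*-test and the sample size arithmetic are not challenged. The power table rests on an assumed range and does not show that the trial is underpowered.

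This should be corrected, because the objective sets what the report may claim. It is wrong as written, not a detail left to a fuller document.

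**What to change.** 1. In Primary objective and Study design, state the comparison as ropivacaine versus saline through MOTAP catheters, both groups receiving IV PCA hydromorphone, and celecoxib where eligible.
2. In Secondary objectives, change the stem to the effect of ropivacaine given via MOTAP catheters.
3. Add one sentence saying that no randomised comparison with PCA without catheters is made, and that no between-arm difference in complications is therefore not evidence of catheter safety against standard care.
4. Optionally, report catheter-related events pooled over both arms as an incidence with an exact 95% confidence interval.

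The cost is a few sentences, plus one descriptive table if item 4 is adopted. Randomisation, treatment, data collection, the primary test and the sample size are unchanged. The price is a narrower claim.

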### Secondary objectives

To assess the effect of MOTAP catheters on:

1. Postoperative pain intensity.

2. Opioid-related adverse effects, including nausea, vomiting, pruritus, sedation, and postoperative ileus.

3. Time to ambulation, duration of hospital stay and reduced postoperative pain disability.

4. Post-surgical complications (for example, pneumonia).

5. Incidence and intensity of chronic postsurgical pain.

## Methods/design

### Study design

This is a multicentre, prospective, blinded, randomized controlled trial comparing MOTAP catheters plus IV PCA to standard care (IV PCA alone) in patients undergoing subcostal incision for liver resection. Full inclusion and exclusion criteria for the trial are summarized in Table 
1. The trial has been approved by the Toronto Academic Health Sciences Network Research Ethics Boards from Sunnybrook Health Sciences Centre (178–2013) and from the University Health Network (12-0493-A).

**Table 1 T1:** MOTAP study inclusion and exclusion criteria

**Inclusion criteria**	**Exclusion criteria**
• >18 years of age	• Patients unable to comprehend instructions, consent, or co-operate with pain assessment
• Undergoing liver resection using a subcostal incision (upper midline extension is allowed)	
• Incision extends to allow visualization of internal oblique and transversus abdominis muscles	• Allergy to any study medications
	• Patient not able to be extubated postoperatively for any clinical reason
	• Laparoscopic surgery
	• Co-existing epidural or intrathecal analgesia
	• Chronic pain disorders or on long-term opioids (greater than 1 month prior to operation)
	• History of substance or alcohol abuse
	• Transplant donor liver resections
	Prior right subcostal incision

MOTAP, medial open transversus abdominis plane.

### Recruitment

Patients meeting the eligibility criteria will be recruited at the preoperative surgical consent visit or the anaesthesia pre-assessment clinic. Information pamphlets will be provided and written informed consent will be obtained. At the time of enrolment, patients will complete baseline questionnaires: the ‘Preoperative Current Pain and Pain History Questionnaire’, Numeric Rating Scale (NRS)
[30] for Pain Intensity and Pain Unpleasantness, the Pain Catastrophizing Scale (PCS)
[31], the McGill Pain Questionnaire - Short Form-2 (SF-MPQ-2)
[32,33], and the Hospital Anxiety and Depression Scale (HADS)
[34].

### Randomization

Patients will be randomized to one of two parallel groups: experimental (local anaesthetic through MOTAP catheter) or placebo (normal saline through MOTAP catheter). Each research pharmacy will have a concealed randomization list and the appropriate syringes will be dispensed by the pharmacy. The code will be retained centrally and only revealed to the investigators once recruitment and data collection is completed. Randomization will be stratified by centre. A brief schema and study outline of this trial is summarized in Figure 
1.

